## Abstract

**Background:**

Cancer-related insomnia (CRI) is one of the most prevalent complaints among cancer survivors and severely impairs patients’ quality of life. As a popular non-pharmacological alternative treatment, acupuncture provides a good clinical curative effect on insomnia. The aim of this trial is to evaluate efficacy and safety of electro-acupuncture on insomnia in patients with lung cancer.

**Method:**

This is a protocol for a multicenter randomized single-blinded sham-controlled trial. We will randomly assign 252 eligible patients with lung cancer-related insomnia into two groups at a ratio of 1:1, the treatment group (EA) and the control group (sham EA). All treatment will be given 3 times per week for 8 weeks, and a 12-week follow-up will be conducted. The primary outcome will be measured by the Pittsburgh Sleep Quality Index (PSQI). The secondary outcomes will include sleep parameters recorded from the actigraphy, scores from Quality of Life Questionnaire Core-30 (QLQ-C30), and Patient Health Questionnaire-9 (PHQ-9). All adverse effects during the trial will be assessed by the Treatment Emergent Symptom Scale (TESS). All analyses will be based on ITT principle and performed with the statistical software SPSS (version 24.0) by *t* test, rank-sum test, chi-square, and so on. A two-sided significance level will be set at 5%.

**Discussion:**

This large-sample trial protocol will evaluate the efficacy of electro-acupuncture on insomnia in patients with lung cancer. This protocol, if proven to be effective, will contribute to filling the gap in treatment options in the CRI field and provide a promising intervention for insomnia in lung cancer survivors.

**Trial registration:**

ChiCTR ChiCTR1900026395. Registered on 8 October 2019, http://www.chictr.org.cn/showproj.aspx?proj=44068

## Background

Cancer-related insomnia (CRI) is one of the most prevalent complaints among cancer survivors, especially in the lung, breast, head, and neck cancers [1]. Lung cancer has the highest prevalence of incidence and mortality of malignant tumors in China. It is expected that by 2020, the incidence of lung cancer will exceed 800,000 and the death toll will approach 700,000 in China alone [2]. According to Wei’s research [3], the incidents of cancer-related insomnia among lung cancer patients has risen up to 68.4%. Concurrently, foreign researchers [4, 5] have shown that lung cancer patients have a relatively high incident rate of all sleep-related problems when compared with all other cancer types. The causative link between cancer survivors and increased incidents of insomnia remains uncertain and may consist of complex interactions of various factors. Savard and Morin [6] divided the etiology into three main categories: predisposing, precipitating, and perpetuating factors. Different pathological types and clinical stages also have significant effects on CRI as well as symptoms induced by cancer and adverse effects created by anti-cancer therapies. CRI is a frequently overlooked consequence of cancer diagnosis and treatment [7], mainly manifesting as difficulty in initiating sleep or maintaining sleep, waking up earlier than desired, and patient’s resistance to go to bed on an appropriate schedule. It results in negative effects, such as fatigue, attention impairment, irritability, and daytime sleepiness, all of which severely impairs the overall quality of life and even prognosis of cancers [8]. Therefore, lung cancer-related insomnia is an important problem to be solved among the lung cancer survivors.

At present, pharmaceutical therapy is the most common therapy for management of insomnia with lung cancer, such as benzodiazepines (e.g., clonazepam, midazolam) and non-benzodiazepines (e.g., zolpione, zalepron). Although pharmacotherapy shows good short-term curative effect, long-term large doses are not recommended due to drug resistance, psychological dependence, and physical dependence [9]. Meanwhile, the efficacy and safety of its interaction with anti-tumor drugs is not confirmed. Therefore, many patients refuse hypnotics, for they can impair the overall quality of life and even prognosis of tumors. In addition to pharmaceutical therapy, Cognitive Behavioral Therapy (CBT), exercise intervention, and herbal medicine are applied in clinic as primary treatments; however, all lack valid evidence to confirm their efficacy and safety. Therefore, it is imperative to find a safe, effective therapy with few side effects, as currently, there is a dearth of effective methods to treat insomnia related to lung cancer.

Acupuncture has showed an increasing prevalence all over the world, and its definite curative effect is widely recognized by countless patients. As an acknowledged complementary treatment, acupuncture is a non-pharmacological method in treating various common disease, including insomnia, depression, headache, back pain, facial paralysis, and so on. In addition, acupuncture also shows its obvious effect in intractable diseases, such as Parkinson’s disease, cerebral infarction, ankylosing spondylitis, and so on [10]. As a mature technology, eletro-acupuncture device has already been standardized by National Medical Product Administration in China. As a safe and effective treatment method, EA is widely accepted by patients and applied in clinic with the advantages of long-term stimulation, easy to control the intensity of stimulation, and efficacy of enhancing the needling sensation. It can adjust the biological dysfunctional of human body and has the effects of relieving pain, inducing sedation, and promoting the circulation of qi and blood, particularly suitable for insomnia. According to various researches, acupuncture provides a good clinical curative effect on insomnia, takes effect quickly, and is relatively safe with few side effects. Previous studies [10] have provided evidence that acupuncture has effects on sleep disorders in general population, but there are few high-quality studies focused on acupuncture as a method for the treatment of lung cancer-related insomnia. We will take the lead to prove the safety and efficacy of acupuncture as a treatment of insomnia in lung cancer patients. Otte et al. [11] carried out a single group clinical trial, applying actigraphy as the main outcome measurement. After three sessions of acupuncture treatment, sleep duration and sleep efficiency were significantly improved among 10 breast cancer patients. There are two studies on the effects of acupuncture on depression symptoms [12] and hot flashes in cancer survivors [13]. But it is uncertain that acupuncture has the curative effect on CRI, for that sleep-related measurement is only a secondary outcome in these studies. Song et al. [14] have carried out a large-sample randomized controlled trials of acupuncture on treatment of CRI, which divided into two groups: treatment group with acupuncture and control group that received estazolam and no acupuncture. The trial result showed that there were no statistical differences between the two groups in the sleep efficiency during the treating period. However, this trial exhibited some nullifying deficiencies, including such confounding factors as no restrictions to cancer types and no detailed refinement of inclusive criteria and treatment methods [15]. Therefore, rigorous high-quality and well-designed RCTs with large samples are urgently needed to prove the safety and efficacy of acupuncture treatment on insomnia in lung cancer patients. These contributions will lay a solid foundation for further promotion and application of acupuncture in the future.

We therefore designed this large-sample multicenter randomized controlled trial with rigorous methods, effective randomization, accurate statistical analysis, and valid measures. We hypothesized that electro-acupuncture is an effective and safe method in treating insomnia among lung cancer patients. The objectives of this trial are:
To evaluate efficacy of electro-acupuncture on insomnia in lung cancer patients as measured by PSQI scores, data from actigraphy, and dose of hypnotics compared with sham EA.To evaluate safety of eletro-acupuncture compared with shame EA by number of adverse events, number of dropout, and the reasons both in treatment group and sham group.To determine whether EA can relieve depression and improve quality of life in lung cancer patients as measured by PHQ-9 scores, QLQ-C30 to compare the between-group difference.

## Methods

### Study design

This is a study protocol of a multicenter randomized patient-and-assessor-blinded sham-controlled clinical trial designed to evaluate the safety and efficacy of electro-acupuncture on insomnia in patients with lung cancer. A total of 252 eligible outpatients and in-patients with lung cancer-related insomnia will be recruited from three hospitals in Shanghai: Shanghai Municipal Hospital of Traditional Chinese Medicine (TCM), Shanghai Chest Hospital, and Putuo District Central Hospital. Each participant will be informed of study-related information and sign a written informed consent before they enter the trial. They will then be randomly divided into treatment group and control group at a ratio of 1:1, receiving EA and sham EA 3 times per week for 8 weeks respectively. The schedule of enrollment, intervention, and assessment is presented in Table 1. This trial is strictly designed to follow the Consolidated Standards of Reporting Trials (CONSORT) statement and Standards for Reporting Intervention in Controlled Trials of Acupuncture (STRICTA) [16] recommendations. The flowchart of the trial is presented in Fig. 1, and the study design schedule is presented in Table 1.

**Table 1 Tab1:** Study design schedule

Period week(W)	Enrollment	Allocation	Treatment			Follow-up	
	Week − 1	Week 0	Week 1	Week 4	Week 8	Week 12	Week 20
Enrollment	**×**						
Informed consent	**×**						
Medical history	**×**						
Merger disease	**×**						
Randomization		**×**					
Intervention			**×**	**×**	**×**		
Primary outcome							
PSQI	**×**	**×**		**×**	**×**	**×**	**×**
Secondary outcomes							
Actigraphy		**×**			**×**		
QLQ-C30		**×**			**×**		
PHQ-9		**×**			**×**		
Dose of hypnotics		**×**	**×**	**×**	**×**	**×**	**×**
Adverse event monitoring (side effects and complications)	**×**	**×**	**×**	**×**	**×**	**×**	**×**
Assessment of credibility		**×**					
Assessment of blinding success			**×**		**×**

**Fig. 1 Fig1:**
[figure not shown]
Study flowchart

### Participants

#### Recruitment

This multicenter randomized controlled trial will be conducted in Shanghai Municipal Hospital of Traditional Chinese Medicine (TCM), Shanghai Chest Hospital, and Putuo District Central Hospital. We plan to recruit 252 participants in total through online and offline advertisement inside and outside these hospitals. Patients who have interest in entering this trial can phone the researchers or communicate with them face to face for more study details. The researchers will screen patients according to the inclusion and exclusion criteria and then thoroughly inform the patients of benefits gained from this trial and potential adverse reactions. Eligible participants will be proceeded with the intervention and assessments after signing informed consent.

#### Inclusion criteria

Male or female patients aged between 19 and 70 years oldDiagnosed with stage I–IIIA pulmonary malignancy according to imaging result, histologic examination, and TNM classificationContinuous insomnia related to lung cancer treatment or cancer itself for at least 3 months, and meets the diagnostic criteria of chronic insomnia according to The Diagnostic and Statistical Manual of Mental Disorders, Fifth Edition (DSM-V), American Psychiatric Association (APA)An Eastern Cooperation Oncology Group (ECOG) performance status of less than 2Score of Pittsburgh Sleep Quality Index (PSQI) of more than 11Have never received acupuncture treatmentWilling to participate in the trial and provide written consent

#### Exclusion criteria

A plan for surgery or chemotherapy during the trialA diagnosis of secondary insomnia caused by depression, anxiety or other psychiatric disorders, and addition of caffeine, alcohol, or drugsIndex of cancer pain measured by the numeric rating scale ≥ 4A diagnosis of severe cognitive deficit failing to cooperateA diagnosis of severe diseases of the cardiovascular, hepatic, renal, cerebrovascular, or hematopoietic systemsAcupuncture area with skin infection, ulcer, and soarsPregnant or breastfeeding womenHaving participated in other clinic trials within 4 weeks of the beginning of this trial

#### Randomization and allocation concealment

This trial will adopt stratified, variable block randomization method with setting a random block size as 2, 4, or 6. An independent researcher, who has no contact with participants, assessors, and acupuncturists, will use SPSS (version 24.0) to generate random numbers with the randomized blocks, dividing 252 participants into two groups at a ratio of 1:1: treatment group and sham group, and randomly allocate them into three different hospitals: Shanghai Municipal Hospital of Traditional Chinese Medicine (TCM), Shanghai Chest Hospital, and Putuo District Central Hospital. The researcher will make random allocation cards, each with its allocated hospital and group recorded, and seal each card into an opaque envelope, which will not be revealed until the first acupuncture treatment.

#### Blinding

This is a single-blinded (patient-assessor-blinded) study. Before treatment, all participants will be informed that they will be assigned to either EA group or sham EA group. They will also be required to wear eye-patch in a private quiet space during the whole treatment period. The principal researcher, assistant researchers, data analysts, assessors, and statisticians will all be blinded to the group allocation. Only the acupuncturist will know their allocated groups, but they will not be informed of any qualitative information on the patient, including severity of lung cancer-related insomnia, merger disease, or dose of hypnotics. This trial will set up a data safety monitoring committee according to the guidance of Data Safety Monitoring Board (DSMB). Experts in the committee will be responsible for monitoring the data safety and have the right to reveal blinded data.

### Interventions

Participants will receive either EA or sham EA, three times per week for 8 weeks, and the follow-up period will be 3 months. Only a licensed acupuncturist with more than 2 years of clinical experience will be responsible for performing the real and sham acupuncture treatment. All manipulation should adhere to the STRICTA. Every treatment session will last for 30 min in a private quiet space, with each participant wearing an eye-patch and in a lying position.

#### Electro-acupuncture (EA) treatment

Participants in treatment group will receive real electro-acupuncture treatment. Stainless steel 0.25 × 40 mm acupuncture needles (Wuxi Jiajian Medical Material Co., Ltd., Wuxi, China) will be inserted into 15 acupoints, including 11 core acupoints and 4 additional acupoints. The core acupoints are GV20 (Baihui), GV24 (Shenting), GV29 (Yintang), bilateral EX-HN22 (Anmian), HT7 (Shenmen), SP6 (Sanyinjiao), and ST36 (Zusanli), and the additional acupoints should be chosen from the following points: LR3 (Taichong), KI3 (Taixi), PC6 (Neiguan), CV4 (Guanyuan), CV12 (Zhongwan), LR14 (Qimen), ST44 (Neiting), and LR2 (Xingjian), based on syndrome differentiation of participants. The locations, indications, and manipulation methods are specifically presented in Table 2. After the needle is inserted to a certain depth of points, it will be manipulated with needling techniques including lifting and thrusting or rotating methods for Deqi sensation. After Deqi, the electro-acupuncture device (CMNS6-1, Wuxi Jiajian Medical Device Co., Ltd., China) will be applied connecting to points GV20 (Baihui), GV29 (Yintang), bilateral SP6 (Sanyinjiao), and ST36 (Zusanli) with 3-Hz frequency and the varying amplitude depending on the comfort of the participant which will be limited between 2 and 5 mA, to strengthen the needling sensation.

**Table 2 Tab2:** Location, indication, and methods of acupoints for treating lung cancer-related insomnia

Acupoints	Location	Method
GV20 (Baihui)	5 *cun* directly above the midpoint of the anterior hairline, at the midpoint of the line connecting the apexes of the two auricles.	Subcutaneous insertion 16–26 mm. Moxibustion can be used for reinforcing Yang.
GV24 (Shenting)	0.5 *cun* directly above the midpoint of the anterior hairline.	Subcutaneous insertion 16–26 mm.
GV29 (Yintang)	On the forehead, at the midpoint between the two medial ends of the eyebrow.	Subcutaneous insertion 10–16 mm.
EX-HN22 (Anmian)	At the midpoint between Fengchi and Yifeng, at the middle of sternocleidomastoid tendon.	Perpendicular insertion 33–49 mm.
HT7 (Shenmen)	At the ulnar end of the transverse crease of the wrist, in the depression on the radial side of the tendon of m. flexor carpi ulnaris	Perpendicular insertion 10–16 mm.
SP6 (Sanyinjiao)	3 *cun* above the medial malleolus, on the posterior border of the medial aspect of tibia.	Perpendicular insertion 33–49 mm.
ST36 (Zusanli)	3 *cun* below Dubi (ST35), one finger-breadth (middle finger) from the anterior crest of tibia	Perpendicular insertion 33–66 mm
LR3 (Taichong)	On the dorsum of the foot, in the depression proximal to the first metatarsal space.	Perpendicular insertion 16–26 mm
PC6 (Neiguan)	2 *cun* above the transverse crease of the wrist, on the line connecting Quze (PC3) and Daling (PC7), between the tendon of m. palmaris longus and m. flexor carpi radialis.	Perpendicular or oblique insertion 16–33 mm.
KI3 (Taixi)	Posterior to the medial malleolus, in the depression between the tip of the medial malleolus and tendo calcaneus.	Perpendicular or oblique insertion 16–33 mm
CV4 (Guanyuan)	On the anterior midline, 3 *cun* below the umbilicus	Perpendicular or oblique insertion 33–40 mm. This point is often used for moxibustion for tonification.
CV12 (Zhongwan)	On the anterior midline, 4 *cun* above the umbilicus.	Perpendicular or oblique insertion 33–40 mm.
LR14 (Qimen)	Directly below the nipple, in the sixth intercostal space, 4 *cun* lateral to the anteri or midline	Oblique or subcutaneous insertion 16–26 mm
ST44 (Neiting)	Proximal to the web margin between the second and third toes, at the junction of red and white skin	Perpendicular or oblique insertion 16–26 mm
LR2 (Xingjian)	On the dorsum of the foot, proximal to the margin of the web between the first and second toes.	Perpendicular or oblique insertion 16–26 mm

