#### Sham EA control

Participants in the control group will receive sham electro-acupuncture treatment at the same acupoints as the treatment group with a blunt tipped placebo needle named Streitberger placebo needle from Germany [17]. This kind of needle can move inside the handle and appear to be shortened after puncturing without penetrating the skin. Participants will find it difficult to distinguish the placebo needle and real acupuncture needle because of the similar sensation and appearance. The electro-acupuncture device will be connected to points, GV20, GV29, bilateral SP6, and ST36 without any electrical current.

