##### Assessment of the subject blinding success rate

All participants will receive the blinding test twice in week 1 and week 8 to assess the success rate of subject blinding. The question is “When you are volunteered for the trial, you were informed that you have the equal chance of receiving traditional acupuncture and acupuncture-like stimulation treatment. Which one do you think you have received?” Participants should choose one of the three answers: acupuncture treatment, acupuncture-like stimulation treatment, or uncertain.

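### Table 2 permits optional moxibustion at core point GV20 in the EA arm, and the sham procedure has no counterpart

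*Protocol article*

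**What the plan says.** The Interventions section gives two regimens and no third element: "Participants will receive either EA or sham EA, three times per week for 8 weeks". The section on EA treatment lists GV20 first among the core acupoints and then refers the reader to the table: "The locations, indications, and manipulation methods are specifically presented in Table 2". The steps it describes are needle insertion, manual manipulation to obtain Deqi, and current applied at named points.

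In Table 2, the Method cell for GV20 gives an insertion direction and depth and then adds: "Moxibustion can be used for reinforcing Yang". The cell for CV4, an additional point, carries a looser comment: "This point is often used for moxibustion for tonification". The other 13 of the 15 rows give only insertion direction and depth.

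Under Sham EA control, control participants "will receive sham electro-acupuncture treatment at the same acupoints as the treatment group with a blunt tipped placebo needle". The stimulator is connected at the same points but delivers no current. Moxibustion is not mentioned. On who knows the allocation, the Blinding section says: "Only the acupuncturist will know their allocated groups".

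**The concern.** The Discussion says the two-arm design is meant to separate a real effect of electro-acupuncture from placebo. That works only if the arms differ in needle penetration and current and in nothing else. Moxibustion is neither. If it is given in the EA arm, an EA-versus-sham difference can no longer be credited to EA alone.

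Blinding is also at stake. PSQI, the primary outcome, is self-rated, so it depends on patients not knowing their arm. The eye-patch blocks sight but not warmth or smell. The protocol tests patient blinding ("All participants will receive the blinding test twice in week 1 and week 8"), but that test would at best show a loss of blinding, not prevent it.

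The option has no criterion, dose or frequency, and the trial runs in three hospitals. The Quality control section itself warns that practitioners who interpret acupuncture methods differently may introduce treatment bias, and the Discussion promises standardized manipulation. An undefined optional step in the methods table works against both.

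**Working it through.** No power or sample-size figure depends on this point. The check compares the relevant sections and counts how far the permission extends.

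**1. Is GV20 used in every EA participant?** The EA section states 11 core acupoints. Three lie on the midline (GV20, GV24, GV29) and four are bilateral (EX-HN22, HT7, SP6, ST36): 3 + 4 × 2 = 11. This reproduces the stated count. GV20 is therefore a fixed point for 126 of 126 EA participants (100%).

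**2. Does the text permit moxibustion there?** The wording at GV20 is permissive and sits in the Method column of the table that the EA section designates for methods. The wording at CV4 only describes common practice. CV4 is 1 of 8 candidate additional points, of which 4 are chosen per patient, so it would not reach everyone in any case. The finding rests on GV20.

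**3. Is there a sham counterpart?**

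| Element | EA arm | Sham arm |
|---|---|---|
| Points | 11 core + 4 additional | Same points |
| Needle | Penetrating | Non-penetrating placebo |
| Device | Connected, current on | Connected, no current |
| Moxibustion at GV20 | Optional (Table 2) | Not mentioned, real or simulated |

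The first three rows are matched by design. The fourth is not.

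**4. Who would decide?** The acupuncturist delivers the treatment and is the one person stated to know the arm, so the option can be used selectively in EA participants.

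**5. Reach.** Sessions per participant: 3 per week × 8 weeks = 24. Across the EA arm: 126 × 24 = 3,024 planned sessions in which the option is open, against 0 in the sham arm.

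**6. Possible bias.** Suppose a fraction *p* of EA participants received moxibustion and it changed their PSQI by *m* points on average, additively. The EA-versus-sham difference would then shift by *p* × *m*. The documents give neither *p* nor *m*, so no value can be set against the planned difference of 2.0.

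**The case against.** The strongest reply is that Table 2 is partly general acupoint reference rather than a literal instruction sheet. The EA section fixes a 40 mm needle for all points, yet the table gives depths up to 49 mm at EX-HN22 and SP6 and up to 66 mm at ST36, which that needle cannot reach. The CV4 comment is plainly general lore, and the GV20 remark may be the same. The caption and the EA section also promise indications, but no separate indication column appears in the text available, so the remark may be indication text that ended up in the Method cell. The running text gives a complete regimen without moxibustion and names no material, timing or criterion for it. Acupuncturists are trained on the interventions. The Quality control section refers to treatments the protocol contraindicates, so the full protocol may already exclude moxibustion.

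Much of this stands. It makes actual use less likely and supports reading the remark as unintended. It does not remove the permission: no other section of the article overrides the GV20 cell. Tailoring by syndrome differentiation, which the protocol endorses, also makes a remark about reinforcing Yang readable as a usable indication. If the full protocol does prohibit moxibustion, Table 2 contradicts it. The point rests on a permission that is stated, not on a prohibition that is missing.

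One could also argue that using the same acupoints in the sham arm carries Table 2 over to it. But the sham section extends the points, not the methods, and insertion depths cannot apply to a non-penetrating needle. Even on that reading, a treatment that is not EA would be optional in both arms at an unblinded operator's discretion.

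**Conclusion.** The concern holds. As written, the plan allows an unmatched active co-intervention in the EA arm, and this conflicts with the regimen in its own running text. Any use would confound the EA-versus-sham contrast and could unblind patients who rate the primary outcome themselves. Because Table 2 permits it, use would not clearly count as a major violation, so the Per-Protocol Set could not be relied on to exclude affected participants.

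The size of any bias is unknown. The conclusion assumes that the Method column is read as instruction, as the EA section directs. Confidence is medium, because the remark may be accidental and never acted on. It should be corrected.

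**What to change.** Delete the moxibustion remarks at GV20 and CV4 from Table 2. State that moxibustion is not allowed in either arm during the trial; if the full protocol already lists it as disallowed, bring Table 2 into line with that list. Record any use in the case report form as a protocol deviation.

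The cost is two remarks removed, one sentence added and one deviation item in the case report form. No extra staff, visits or participants are needed.
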